# Efficacy of brief behavioral counselling by allied health professionals to promote physical activity in people with peripheral arterial disease (BIPP): study protocol for a multi-center randomized controlled trial

**DOI:** 10.1186/s12889-016-3801-7

**Published:** 2016-11-09

**Keywords:** Exercise, Physical inactivity, Intermittent claudication, Cardiovascular disease, Health counselling, Quality of life, Cost effectiveness, Biomarkers, Multi-disciplinary, Behavioral health

## Abstract

**Background:**

Physical activity is recommended for people with peripheral arterial disease (PAD), and can improve walking capacity and quality of life; and reduce pain, requirement for surgery and cardiovascular events. This trial will assess the efficacy of a brief behavioral counselling intervention delivered by allied health professionals to improve physical activity in people with PAD.

**Methods:**

This is a multi-center randomised controlled trial in four cities across Australia. Participants (*N* = 200) will be recruited from specialist vascular clinics, general practitioners and research databases and randomised to either the control or intervention group. Both groups will receive usual medical care, a written PAD management information sheet including advice to walk, and four individualised contacts from a protocol-trained allied health professional over 3 months (weeks 1, 2, 6, 12). The control group will receive four 15-min telephone calls with general discussion about PAD symptoms and health and wellbeing. The intervention group will receive behavioral counselling via two 1-h face-to-face sessions and two 15-min telephone calls. The counselling is based on the 5A framework and will promote interval walking for 3 × 40 min/week. Assessments will be conducted at baseline, and 4, 12 and 24 months by staff blinded to participant allocation. Objectively assessed outcomes include physical activity (primary), sedentary behavior, lower limb body function, walking capacity, cardiorespiratory fitness, event-based claudication index, vascular interventions, clinical events, cardiovascular function, circulating markers, and anthropometric measures. Self-reported outcomes include physical activity and sedentary behavior, walking ability, pain severity, and health-related quality of life. Data will be analysed using an intention-to-treat approach. An economic evaluation will assess whether embedding the intervention into routine care would likely be value for money. A cost-effectiveness analysis will estimate change in cost per change in activity indicators due to the intervention, and a cost-utility analysis will assess change in cost per quality-adjusted life year. A full uncertainty analysis will be undertaken, including a value of information analysis, to evaluate the economic case for further research.

**Discussion:**

This trial will evaluate the efficacy and cost-effectiveness of a brief behavioral counselling intervention for a common cardiovascular disease with significant burden.

**Trial registration:**

ACTRN 12614000592640 Australian New Zealand Clinical Trials Registry. Registration Date 4 June 2014.

**Electronic supplementary material:**

The online version of this article (doi:10.1186/s12889-016-3801-7) contains supplementary material, which is available to authorized users.

## Background

Peripheral artery disease (PAD) is the narrowing or blockage of the lower limb arteries usually due to atherosclerosis and associated thrombosis [1]. This reduces blood flow to the limbs, with the most recognised symptom being leg pain that typically presents during walking, worsens with exertion, and is relieved by rest (intermittent claudication: IC). Maximal walking capacity in people with PAD is less than 50 % of that in age-matched controls, and the functional limitations are similar to those seen in people with severe heart failure [2]. People with PAD and IC typically avoid walking and related activities, which constrains social and role functioning and activities of daily living, and precipitates poor quality of life and accelerated functional decline [3]. This, in turn, predisposes them to high health service utilisation and associated costs [4–11], and premature mortality [12]. As an indicator of systemic atherosclerosis, PAD is positively associated with other cardiovascular diseases, coronary events and stroke [13], with one meta-analysis suggesting a two-fold increased risk of mortality, cardiovascular mortality and major coronary events over 10 years [14]. Coronary heart and cerebrovascular events account for ~65 % of deaths in people with PAD, with a two year prospective study suggesting a 70 % increased risk of cardiovascular events and an 80 % increased risk of death compared to people with coronary artery disease alone [13].

PAD is a common chronic disease associated with ageing. Prevalence has been reported as 8.3 % in people aged 60–69 years [6], 14.5 % in those aged >70 years [15] and 40 % of people aged >80 years [16]. The economic burden of PAD is substantial, as reflected by expensive vascular surgical interventions aimed at opening or bypassing blocked arteries, and recurring hospitalisations [7]. A total of USD$4.37 billion was spent on PAD-related treatment in 2001, with 88 % for inpatient care [17]. Prior lower limb revascularisation is associated with high hospitalisation costs and rates of subsequent procedures during the following 2 years [7]. Rates of surgical intervention are increasing dramatically: There was a 43 % increase between 2000 and 2008 in Australia which far exceeds the estimated growth in the number of people with PAD [18]. Such interventions have limited durability, are expensive to perform and their value in providing sustained improvement in quality of life and reducing subsequent morbidity and mortality is not well established [19, 20]. Given the high prevalence and burden of PAD, and the large expense and limited durability of surgical interventions, there is an urgent need to identify effective, affordable and sustainable alternative management options.

International guidelines for PAD management recommend exercise [21–24], and typically identify three 40-min sessions per week of interval walking at maximum tolerable speed (i.e., moderate pain level with rest periods) [2, 25]. There is good evidence that supervised exercise is as effective as surgical procedures in improving walking ability in patients that have IC [20, 26, 27]. Supervised exercise programs have been shown to improve walking capacity, functional mobility, maximal walking distance, pain symptoms and health-related quality of life; and to reduce leg pain and cardiovascular risk [20, 28–32]. People with PAD who are physically active have a lower average annual functional decline than those who are inactive [33], and a significantly lower five-year mortality risk [12, 34]. Reduced daily sitting time is associated with a reduced decline in the six minute walk test [35], with improvements in walking capacity and physical functioning enhancing quality of life in people with PAD with IC and people without IC [36]. It is estimated that even small increases in physical activity for people with IC would significantly reduce all-cause mortality [12].

However, an international survey found only 30 % of vascular surgeons had access to supervised exercise programmes for patients with PAD, and of those who did have access, many referred less than half their patients [37]. Patient travel to facility-based supervised exercise sessions is burdensome, and drop-out rates are often high [38–40]. Lack of patient and physician awareness of the role of supervised exercise, and patient barriers of transportation and time contribute to this being an underused treatment [37, 41, 42]. For those surgeons who do not have access to refer to supervised exercise programmes, the usual option is to give brief advice to do walking [37].

However, people with IC have condition-specific barriers to walking that constrain participation. IC is an intense, cramping pain in the lower limbs, and some patients believe this pain is harmful [43], and have low confidence in their walking ability [44, 45]. Patients tend to be unclear about the causes and severity of PAD and the associated cardiovascular risk [43, 46, 47], and are unaware of walking recommendations and the mechanisms by which walking can improve PAD-specific and general health outcomes [43]. The surgical model of care can precipitate beliefs of an acute, treatable condition [43] and little personal control over health outcomes [44, 47]. Illness and treatment beliefs predict adherence to recommended levels of walking in people with PAD with very high accuracy [44]. A willingness to persist with activities given the concurrent pain, and a desire to be functionally competent, are also positively associated with physical mobility in people with PAD [45]. Adaptive self-management beliefs are therefore a key target to enable walking among people with PAD.

Behavioural counselling is a patient-centred approach that can promote adaptive illness- and exercise-related beliefs associated with sustained physical activity behaviour change in people with chronic conditions and cardiovascular risk [48, 49]. Preliminary evidence indicates that counselling can improve physical activity in people with PAD. A program combining weekly cognitive behavioral counselling and walking sessions demonstrated significant improvements in accelerometer assessed physical activity (mean difference 114.7 activity units, 95 % CI 12.82 to 216.5; *P* = .03); 6-min walk distance (mean difference 53.5 m, 95 % confidence interval [CI] 33.2 to 73.8; *P* < .001); Walking Impairment Questionnaire (WIQ) speed score (mean difference 10.4, 95 % CI 3.4 to 17.4; *P* = 0.004) and distance score (mean difference 11.1, 95 % CI 3.9 to 18.1; *P* = 0.003) [50]; and psychosocial indicators of satisfaction with physical functioning, pain acceptance and social functioning [51] relative to a health education control group. There were sustained improvements after 12 months in 6-min walk distance (mean difference 34.1 m, 95 % CI, 14.6 to 53.5; *P* < 0.001) and WIQ speed score (mean difference 8.8, 95 % CI, 1.6 to 16.1; *P* < 0.018) [52]. However, this approach was resource intensive, with weekly sessions delivered over 6 months. A more brief counselling intervention, involving two 1-h sessions of individualised behavioral counselling and two follow up telephone calls by a psychologist, demonstrated a significant increase in pain-free walking distance and daily walking in the intervention versus the control group (usual care plus non-walking related conversation during home visits) after four months, with a mean difference of 1575 pedometer steps/day (95 % CI, 732 to 2419) [53]. At 24 months, the intervention group completed on average 1630 steps/day (95 % CI, 495 to 2765) more than the control group, and significantly more participants in the control group had endovascular or open surgery than in the intervention group (OR 3.09 95 % CI 1.06 to 9.04; *p* = 0.037) [54]. However, as the counselling was delivered by a psychologist in patients’ homes, the wide scale applicability of this approach is not known.

## Methods/Design

### Aim and research questions

The primary aim of this study is to test the efficacy of brief behavioral counselling, delivered by allied health professionals, to increase physical activity in people with PAD. Secondary aims are to examine the effect of the counselling on functional capacity, revascularisation rate, clinical events, and resource use; and to perform an economic evaluation of the counselling intervention compared to usual care. This fills an important gap in the literature on PAD clinical management, and will address the following questionscan brief behavioural counselling be delivered by health professionals who are not qualified psychologists, following training?can the brief behavioural counselling be effectively delivered in a variety of different centres by different professionals?is delivery of the brief behavioural counselling in a health care setting effective in achieving sustained physical activity behaviour change?

### Design and setting

This is a multicentre, prospective, randomised superiority trial with two parallel study groups: a control and an intervention group. The trial will be conducted in four cities across Australia. Study sites will include three specialist vascular management clinics (Townsville, Brisbane, Perth) and a University clinic (Sydney).

### Management

The trial will be overseen by a Trial Steering Committee comprising senior vascular investigators from the centers involved; and experts in trial management, physical activity behavior change, health economics and exercise physiology. This will be the main policy and decision-making committee. Trial coordination will be facilitated by the National Health and Medical Research Council (NHMRC) funded National Centre for Research Excellence in Peripheral Arterial Disease (NCRE-PAD). An independent data management center (CCRE therapeutics, Monash University) will provide a computer generated randomisation list. A study coordinator located at James Cook University will organise activities across the participating sites; assisting with local ethics reports and communication with the local sites (including uniformity of collection and reporting of data, central randomisation, data storage and processing). The training, competency assessment, and supervision of allied health professionals who will deliver the intervention and control group protocol; and the intervention fidelity assessment, will be undertaken by a clinical and health psychologist on the investigatory team (NB).

### Participants

Participants will be recruited from specialist vascular management clinics at The Townsville Hospital, The Royal Brisbane and Womens’ Hospital, and Fremantle Hospital Perth; and from referrals from vascular surgeons and general practitioners in Sydney. Participants will also be recruited from the investigators’ registry of participants involved in prior research studies who have agreed to be re-contacted.

People who express an interest in the study will be screened and enrolled by dedicated assessment staff either in person or by telephone. Inclusion criteria areDiagnosis of PAD by a vascular specialist, including patient-reported symptoms of IC and/or absence of lower limb pulses and/or resting ankle brachial pressure index (ABPI) <0.9 or >1.4 [23];Able to walk without assistance of another personNo current or planned involvement in an organised exercise trial or programNo currently planned peripheral vascular interventionPhysician confirmed ability to participate in the trial (i.e. medically stable, able to walk and undertake physical activity, attend assessments and comprehend the behavioral counselling). Patients with severe PAD, such as rest pain, arterial ulceration or gangrene requiring urgent vascular intervention will be ineligible.

Exclusion criteria arePrevious major lower limb amputation such as above or below kneePatients who report doing more than 120 min of moderate-vigorous structured exercise per week.

### Sample size calculation

We hypothesise that over a 4-month period the intervention will increase physical activity by ~50 %, evidenced by mean daily step counts of 5000 ± 3400 for those receiving the counselling intervention compared to 3300 ± 2200 for those randomised to the control group. We also hypothesise that these effects will be maintained at 12 and 24 months post intervention. The effect size and outcome results estimated are based on data from a previous trial [54]. We require 62 participants per group (power 90 %, alpha 0.05, within-subject between visit correlation 0.6) to detect the hypothesised increase in physical activity. Allowing for maintenance of this increase over 24 months, and a drop out of up to 40 %, we require 100 participants per group. We therefore will aim to recruit a total of 200 people.

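### The sample size paragraph does not add up: 100 per group less 40 % drop-out leaves 60, not the required 62, and 62 does not evidently use the listed 0.6 correlation

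*Protocol article*

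**What the plan says.** The Sample size calculation section of the protocol article plans for "mean daily step counts of 5000 ± 3400 for those receiving the counselling intervention" "compared to 3300 ± 2200 for those randomised to the control group", as the effect expected over 4 months. From this it derives a first number: "We require 62 participants per group (power 90 %, alpha 0.05, within-subject between visit correlation 0.6". The correlation is the last of the inputs listed for that number: "within-subject between visit correlation 0.6) to detect the hypothesised increase in physical activity". It then allows for the effect being maintained over 24 months and inflates for losses: "a drop out of up to 40 %, we require 100 participants per group". The recruitment target follows: "We therefore will aim to recruit a total of 200 people".

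The section does not state the formula, whether alpha is one- or two-sided, the baseline SD, or how the correlation enters. The analysis section (Data management and analyses) plans an intention-to-treat comparison by repeated measures mixed models.

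**The concern.** Two steps in the paragraph can be checked, and both raise a question.

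- **From 62 to 100.** The requirement, the drop-out allowance and the final group size appear in adjacent sentences and should be linked by one division. They are not.
- **From the inputs to 62.** A between-visit correlation of 0.6 is listed as an input. Used to adjust for baseline, it should bring the requirement well below that of a plain two-group comparison. Yet 62 lies almost exactly where the plain comparison puts it.

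What is at stake is how the result is read, not whether the trial is large enough. If the calculation made no use of baseline, the stated 90 % power is just missed when the whole drop-out allowance is used up. If it did, the trial has more power than stated and could detect a smaller difference. The paragraph does not let a reader tell which applies, and this matters if the result is null or smaller than expected.

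**Working it through.** **Inputs (Sample size calculation section).** Means 5000 and 3300, so the difference is 1700 steps/day. SDs 3400 and 2200. Power 90 %, alpha 0.05, correlation 0.6, drop-out up to 40 %. Assumed here: two-sided alpha and 1:1 allocation (the latter implied by 100 per group).

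**Step 1: reproduce 62 without the correlation.**

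- Pooled variance = (3400² + 2200²)/2 = 8,200,000; SD = 2864; standardised difference = 1700/2864 = 0.594.
- Normal formula: n = 2 × 8,200,000 × (1.960 + 1.282)² / 1700² = 59.6, so 60 per group.
- Exact t-test, pooled or Welch: 61 per group.
- One-sided alpha by the normal formula: 48.6, so 49, which is not close to 62.

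The two-sided result of 60 to 61 is near enough to count as reproducing 62, with the 0.6 unused.

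**Step 2: use the correlation.**

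*Baseline-adjusted comparison.* The variance is multiplied by 1 − 0.6² = 0.64. Normal formula: 59.6 × 0.64 = 38.2, so 39; t-test: 40 per group.

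*Change score.* This needs a baseline SD, b, which the article does not give. In each group the variance of the change is b² + s² − 2 × 0.6 × b × s, where s is the stated follow-up SD (3400 or 2200). Averaging the two groups and applying the t-test:

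| Assumed baseline SD (both groups) | n per group |
|---|---|
| 2200 | 43 |
| 2500 | 45 |
| 2864 | 51 |
| 3400 | 62 |

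The shortcut factor 2(1 − 0.6) = 0.8, which sets baseline and follow-up SDs all equal to 2864, gives 49.

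*Other routes.* Averaging three post-baseline visits gives a factor of (1 + 2 × 0.6)/3 = 0.733, and 45 per group with the pooled SD. With 3400 used as the SD in both groups it gives 61.6, so 62 (63 by t-test). That discards the stated control SD of 2200 and does not fit the 4-month hypothesis.

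**Step 3: drop-out.**

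- 100 × (1 − 0.40) = 60, which is below 62.
- 62/(1 − 0.40) = 103.3, so 104 per group, 208 in total.
- 1 − 62/100 = 38 %, the largest loss that leaves 62 of 100.
- 60/(1 − 0.40) = 100 exactly. The inflation may therefore have started from the normal-formula result of 60 rather than from 62.

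**Step 4: size of the effect.** Power for 1700 steps/day, t-test, two-sided 0.05:

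| Analysis | 60 per group | 62 per group |
|---|---|---|
| No baseline | 89.7 % | 90.6 % |
| Change score, factor 0.8 | 95.0 % | 95.6 % |
| Baseline-adjusted | 98.1 % | 98.4 % |

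The normal formula gives 90.2 % at 60 per group without baseline.

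**The case against.** **On 62.** It can fairly be said that 62 is reproduced: the means, SDs, power and alpha alone give 60 to 61. It can also be said that the correlation may have been used, since a change score with a baseline SD of 3400 gives exactly 62 and the formula may be in the full protocol, which is not shown. Both points stand. A reader might infer that the stated inputs cannot give 62 at all, or that the correlation was certainly ignored; the document supports neither. What remains is that reaching 62 with the 0.6 takes an input or a choice that the paragraph does not state.

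**On drop-out.** The gap is two participants per group, probably a rounding mismatch between 60 and 62, and 40 % is an upper limit. It is also introduced together with maintenance to 24 months, whereas the hypothesised effect is at 4 months, where losses are not stated and could be lower. A mixed model also uses data from partly followed participants. All this limits the consequence but does not reconcile the three printed numbers.

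**On the assumed difference.** A reader might take 1700 to be an error, because the Background cites 1575 steps/day at 4 months from the earlier work and, for the later follow-up, "At 24 months, the intervention group completed on average 1630 steps/day" more than control. That does not follow. The planning means are described as based on earlier data, not as equal to those estimates. Both quoted confidence intervals (732 to 2419 and 495 to 2765) contain 1700, and the group-level data are in a source that is not at hand.

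**Conclusion.** The point holds as a minor inconsistency. The drop-out step is wrong as written, whatever formula was used: 62, 40 % and 100 cannot all be true. The consistent statements are 104 per group at 40 %, or 38 % at 100 per group.

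The link between the inputs and 62 is unclear rather than shown to be wrong. The most natural match leaves the correlation unused (60 to 61). Using it gives about 40 with baseline adjustment, or 43 to 51 for a change score with a baseline SD of 2200 to 2864. This rests on two-sided alpha, a common baseline SD in the two groups, and a single follow-up contrast.

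A reader might go on to infer that the trial is underpowered. The document's own figures do not support that: with 60 per group, power for 1700 steps/day is 89.7 % without baseline and about 98 % with baseline adjustment. No design decision changes.

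**What to change.** Keep N = 200 and correct the paragraph in two places.

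1. **Drop-out.** Either restate the tolerated loss as 38 %, or keep 40 % and say that the remaining 60 per group give 89.7 % power for 1700 steps/day without baseline adjustment.
2. **Correlation.** Either delete the 0.6, or state how it enters (which contrast, which formula, which baseline SD) and restate the required number and power to match. If the contrast is baseline-adjusted, for example, about 40 per group are required, and 60 per group give about 98 % power.

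Stating that alpha is two-sided would complete the correction. The cost is wording only, with no extra participants.

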### Randomisation

Eligible and consenting individuals who complete the baseline assessment will be randomly allocated to the control or intervention group. The allocation sequence will be computer-generated using a random number sequence and allocation will occur in block sizes up to 4 and will be stratified based on ABPI (<0.50, 0.50-0.69, 0.70-0.89, >1.4), study site, and gender. Allocation is concealed by using a central randomisation site, and different project staff for assessment and allocation/intervention delivery. Participants will be blinded to allocation and the investigators’ hypotheses. Intervention staff will conduct both intervention and control participant contacts, and therefore cannot be blinded to allocation. They will be instructed not to disclose the allocation status to either the participants or assessment staff.

